### Statistical methods

Categorical data will be presented as absolute and relative frequencies, and interval data will be presented as mean and standard deviation or median and interquartile range, as appropriate. Baseline data will be tabulated and compared qualitatively and quantitatively. The primary analysis includes an intention-to-treat comparison of the primary and secondary endpoints. The primary endpoint is dichotomous and will be treated accordingly. We assess the effect of the intervention by calculating a relative risk with a 95% confidence interval. To test the null hypothesis of no difference between the groups we will use the Fisher’s exact test. For the secondary endpoint change in proteinuria, as indicated by albumin/creatinine and protein/creatinine ratio, we will compare the individual regression slopes from baseline to study end in these variables between intervention and placebo group; we will calculate differences and 95% confidence intervals. For hypothesis testing, we will use an unpaired sample t test if a normal distribution can be sensibly assumed, otherwise the Mann-Whitney U test will be used. Adverse events (AE) will be dichotomized and analyzed like the primary endpoint. Secondary analysis will be performed if baseline differences should be noted. In this case we will use multivariable regression methods to adjust for such baseline differences. For data management, range and consistency checks, and analyses we will use Excel (Microsoft, Redmond, WA, USA) and Stata 11 (Stata Corp. College Station, TX, USA). No *a priori* subgroup analyses are planned. An interim analysis is not scheduled. To test for a possible dependency of GFR on the effect of SIR in these patients we will perform an explorative interaction analysis.

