### Number of subjects and level of significance

The calculation of the sample size is based on the results of the most comprehensive follow-up of ADPKD patients with advanced kidney disease. With a mean baseline creatinine of 3 mg/dL, or a mean eGFR of 23 mL/min per 1.73 m^2^, respectively, 40.5% of 142 patients showed a doubling of serum creatinine or dialysis after a mean follow-up of 2.3 years [15]. However, with less than 1.5 fold increase instead of 2 fold increase in creatinine we used a stricter criterion for a favorable outcome, and therefore set our expected outcome probability in the control group at 50%. Formally 31 patients in each group are necessary to demonstrate a clinically meaningful reduction of 50 to 90% of the primary endpoint at an α = 0.05 with a power of 80%. To allow for loss to follow-up, we increase this formal sample size by 10%. Therefore we plan to include 34 patients per group or 68 patients overall into our study. Generally a probability (*P*) value of less than 0.05 is considered statistically significant.

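### Fisher's exact test is valid but conservative at 31 to 34 per group; an unconditional exact test would recover up to 9 points of power at no cost in error control

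*Protocol article*

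**What the plan says.** The Statistical methods section gives the primary endpoint an estimate and a test. The estimate: "We assess the effect of the intervention by calculating a relative risk with a 95% confidence interval". The test: "To test the null hypothesis of no difference between the groups we will use the Fisher’s exact test". The method for the interval is not named, and neither is the sidedness of the test. Adverse events are to be dichotomised and handled in the same way. The software named is Excel and Stata 11.

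The section on the number of subjects supplies the planning figures. The authors "set our expected outcome probability in the control group at 50"%. They then state: "Formally 31 patients in each group are necessary to demonstrate a clinically meaningful reduction of 50 to 90% of the primary endpoint". The error rate given for this calculation is 0.05 and the power is 80%. Enrolment follows from a 10% allowance: "Therefore we plan to include 34 patients per group or 68 patients overall into our study". A P "value of less than 0.05 is considered statistically significant".

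**The concern.** With two binomial arms of about 30, Fisher's test conditions on the total number of events. Few tables are then possible, and the attained error rate falls well below the nominal 5%. A test that uses more of the 5% would detect the same effect more often in the same patients. In a trial of 68 patients that is worth having.

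The second issue is coherence. A log-scale relative-risk interval is not obtained by inverting Fisher's test. In borderline results the p-value and the interval can therefore point in different directions, and the report would have to explain why.

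**Working it through.** **Inputs.** Control event rate 0.50; relative reduction 50 to 90%, so a treated rate from 0.25 down to 0.05; 31 per group formally and 34 enrolled; α = 0.05 (all from the section on the number of subjects). Assumptions: α and the test are two-sided, and the relative-risk interval is the log-scale (Wald) one. Neither is stated.

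**The plan's own figure.** The usual formula is n = [1.96√(2p̄(1−p̄)) + 0.842√(p₁(1−p₁)+p₂(1−p₂))]² / (p₁−p₂)², with p̄ the mean of the two rates.
- 50% vs 25%: (1.342 + 0.557)² / 0.0625 = 57.7, so 58 per group. By enumeration, Fisher's test needs 64.
- 50% vs 5%: (1.238 + 0.459)² / 0.2025 = 14.2, so 15 per group.

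Neither end of the range gives 31. That figure fits a reduction of about 66% with this formula, or about 70% with Fisher's test (79.7% power at 31). The 10% allowance is in order: 31 × 1.1 = 34.1.

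**Size.** All (n+1)² tables were enumerated and the null probability of Fisher p ≤ 0.05 summed over common event rates.
- 31 per group: 2.3% at a rate of 0.2, 3.0% at 0.5; maximum 3.0%.
- 34 per group: maximum 3.0%.

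Boschloo's test rejects when the Fisher p-value is at most c, with c the largest value that keeps the maximum size at or below 5%. Here c = 0.073 at 31 per group (maximum size 4.8%) and c = 0.077 at 34 (maximum size 4.7%). Since c exceeds 0.05, every Fisher rejection is also a Boschloo rejection.

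**Power**, by the same enumeration, control rate 50%:

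| Treated rate | n per group | Fisher | Boschloo | Gain (points) |
|---|---|---|---|---|
| 25% (50% reduction) | 31 | 43.7% | 52.8% | 9.1 |
| 25% | 34 | 49.3% | 55.3% | 6.0 |
| 17% (66% reduction) | 31 | 73.0% | 79.4% | 6.5 |
| 15% (70% reduction) | 31 | 79.7% | 84.9% | 5.2 |
| 5% (90% reduction) | 31 | 98.6% | 99.2% | 0.6 |

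**Test against interval.** Take 16/31 vs 8/31. RR = 8/16 = 0.50. SE(log RR) = √(1/8 − 1/31 + 1/16 − 1/31) = √0.1230 = 0.351. The interval is exp(−0.693 ± 1.96 × 0.351) = 0.25 to 0.99, which excludes 1. Fisher's p = 0.067. This is below c = 0.073, so Boschloo's test rejects.

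The probability that the log-scale interval excludes 1 while Fisher p > 0.05 is, at 50% vs 25%, 6.2% with 31 per group and 3.9% with 34. At 50% vs 5% with 34 per group it is 0.3%.

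Changing the test alone does not settle coherence. With 16/34 vs 8/34, Fisher's p is 0.075, below c = 0.077, so Boschloo's test rejects, while the log-scale interval is 0.25 to 1.01.

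**Zero cells.** At a treated rate of 5%, the chance of no events in the treated arm is 0.95³¹ = 20% (0.95³⁴ = 17%). The log-scale interval is then undefined.

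**The case against.** Fisher's test is a conventional, pre-specified choice, and being conservative is not an error. That stands: type I error is protected, and the point is one of efficiency and coherence. It does not answer the lost power, because the alternative keeps the same guarantee and rejects in every case where Fisher's does.

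Fisher's test may already be built into the sample size, since 31 per group gives 79.7% power at a 70% reduction. That is possible, as the article does not name the method or a single effect. Even so, the same patients would give 84.9% with Boschloo's test.

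Three stronger readings are tempting and not supported.
- A reader might infer a general loss of 9 points. That holds only for 50% vs 25% with 31 per group.
- A reader might infer that test and interval disagree at the planned effect. The plan has no single planned effect. At 34 per group the tables nearest a halving agree: 17 vs 9 (p = 0.080, interval 0.28 to 1.02), 17 vs 8 (0.043, 0.24 to 0.94), 16 vs 8 (0.075, 0.25 to 1.01) and 18 vs 9 (0.046, 0.26 to 0.95). Disagreement also depends on an interval method that the full plan may fix.
- A reader might infer that nothing says which result decides. The Statistical methods section assigns the null hypothesis to Fisher's test, and the sample-size section sets the 0.05 threshold, so the p-value decides.

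**Conclusion.** The point holds as a matter of efficiency. Fisher's test uses at most about 3.0% of the 5% allowed. With 31 per group it gives up between 9.1 points of power (50% reduction) and under 1 point (90% reduction), and 5.2 to 6.5 points at the reductions that 31 per group fits. At the enrolled 34 per group the loss at a 50% reduction is 6.0 points. These figures assume a two-sided test, a 50% control rate and complete data on the stated number per group.

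The disagreement with the interval is secondary. It is conditional on a log-scale method and uncommon even then (6.2% or 3.9% at 50% vs 25%).

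The change does not repair the sample size. At a 50% reduction Boschloo's test reaches only 52.8% (31 per group) or 55.3% (34), far from the stated 80%.

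**What to change.** Before unblinding, replace Fisher's exact test by Boschloo's unconditional exact test (two-sided, 5%) for the unadjusted primary comparison. Report with it a relative-risk interval obtained by inverting a compatible test, by a method that is defined when an arm has no events. The rule that the p-value decides significance can stay as it is. Since adverse events follow the primary analysis, say whether the same pair applies to them; zero counts matter there too.

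The cost is a sentence in the analysis plan, with no extra patients or data, and the error rate stays at or below 5%. The article does not show that Excel or Stata 11 offers these routines, so another package may have to be named. The power stated for a 50% reduction has to be addressed separately in the section on the number of subjects.

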### Enrollment and randomization

Randomization will be performed independent of patient recruitment or inclusion. To yield balanced yet unpredictable groups, we will use a block-randomization scheme in varying blocks of four to six. This randomization list will be provided to the hospital pharmacy for the preparation of the blinded study drugs and otherwise concealed until analysis of the study. Patient ID will be linked to container numbers during the course of the study to warrant allocation concealment. For individual code breaking, we will prepare a set of sequentially numbered sealed opaque envelopes that contain information about treatment allocation. At the end of the study all envelopes will be checked to assess the absence of code breaking. All code breaks will be documented in detail by the study investigators. The randomization code will be broken in the case of any serious adverse event (SAE) if knowledge of the study drug is relevant to the treatment of the SAE. A consecutive number will be assigned to any subject partaking in the study as unique patient identifier code at the time of inclusion.

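### Regression adjustment waits for an observed baseline imbalance instead of always including baseline eGFR, so the valid but conservative unadjusted Fisher test gives up power

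*Protocol article*

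**What the plan says.** Under Statistical methods, the protocol article fixes the primary analysis without conditions. It is by intention to treat, and "The primary endpoint is dichotomous and will be treated accordingly". The effect measure is crude: "We assess the effect of the intervention by calculating a relative risk with a 95% confidence interval". So is the test: "To test the null hypothesis of no difference between the groups we will use the Fisher’s exact test".

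Covariates enter only through a conditional rule. First, "Baseline data will be tabulated and compared qualitatively and quantitatively". Then, "Secondary analysis will be performed if baseline differences should be noted", and "In this case we will use multivariable regression methods to adjust for such baseline differences". The rule covers whichever baseline variables turn out to differ and does not single out eGFR. GFR appears by name only in an exploratory analysis of its interaction with treatment.

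Under Enrollment and randomization, "we will use a block-randomization scheme in varying blocks of four to six"; no stratification by eGFR is mentioned. Table 1 admits any baseline eGFR below 60 mL/min per 1.73 m², excluding only patients who need renal replacement therapy. Under Endpoints, failure is a creatinine rise of more than 1.5-fold, dialysis, transplantation or death within two years.

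**The concern.** Adjustment pays off through the covariate's link with the outcome, which can be judged before the trial. It does not depend on whether the arms happen to differ at baseline. A rule keyed to imbalance therefore leaves a prognostic covariate out of most realised trials. When it does fire, the covariates are those that happened to differ, picked once the baseline table has been seen.

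Here the covariate can be named in advance. With such a wide eGFR range, a fixed relative rise in creatinine means very different absolute losses of function, and patients starting low are also closer to dialysis. In a 68-patient trial with a binary endpoint, both the omitted covariate and a test that runs well below its nominal level cost power that the trial can ill afford.

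**Working it through.** **Inputs from the document.** Control failure rate 50%; relative reduction 50 to 90%; α 0.05; 31 per group, raised to 34 (Number of subjects and level of significance). The same section gives a mean eGFR of 23 in the cohort behind the control rate. **Not in the document, so assumed:** the prognostic strength of baseline eGFR.

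**1. The planned figure.** Exact two-sided Fisher power with 31 per group is 43.7% for 50% vs 25% (a 50% reduction), 79.7% for 50% vs 15% (70%) and 98.6% for 50% vs 5% (90%). The stated 80% is met at about a 70% reduction, not at the lower end of the range. That is a separate point, but 50% vs 25% is where lost power hurts most.

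**2. Actual size of Fisher's test.** This sums the binomial probabilities of all tables with p < 0.05, at 50% in both arms: 3.0% with 31 per arm and 2.6% with 34, against a nominal 5%.

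**3. Boschloo's test instead of Fisher's, still unadjusted.** With 31 per arm the critical Fisher p-value becomes 0.073, with a maximum size of 4.8%. Power for 50% vs 25%:

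| Per arm | Fisher | Boschloo | Gain |
|---|---|---|---|
| 31 | 43.7% | 52.8% | 9.1 points |
| 34 | 49.3% | 55.3% | 6.0 points |

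**4. Why eGFR should be prognostic.** Assume creatinine is proportional to 1/GFR. A 1.5-fold rise then leaves 1/1.5 = 2/3 of GFR. The loss needed to fail is 60/3 = 20 mL/min from 60, but only 23/3 = 7.7 mL/min from 23.

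**5. Always adjusting.** Simulation with 34 per arm and no losses: 4,000 trials per scenario, one standard normal baseline covariate with assumed log-odds per SD, and logistic likelihood-ratio tests (LRT). The Monte Carlo standard error is at most √(0.25/4000) = 0.8 points.

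| Comparison | Log-odds per SD | Fisher | Unadjusted LRT | Adjusted LRT | Gain over unadjusted LRT |
|---|---|---|---|---|---|
| 50% vs 25% | 0.7 | 49.6% | 59.8% | 62.6% | 2.8 |
| 50% vs 25% | 1.0 | 48.4% | 59.0% | 64.6% | 5.6 |
| 50% vs 25% | 1.5 | 49.4% | 60.0% | 72.0% | 12.0 |
| 50% vs 15% | 0.7 | 84.2% | 90.4% | 91.9% | 1.5 |
| 50% vs 15% | 1.0 | 83.7% | 89.8% | 93.8% | 4.0 |
| 50% vs 15% | 1.5 | 83.7% | 89.7% | 95.7% | 6.0 |

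Under the null, the adjusted test rejected in 5.0 to 5.6% of trials.

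A second simulation, with 31 per arm and an assumed eGFR-decline model (eGFR uniform on 15 to 35, failure 51% vs 23%, likelihood-ratio tests calibrated to 5%), gave 56% for Fisher, 65% unadjusted and 67% adjusted. The gain from adjustment there is 2 points.

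**6. What the conditional rule recovers.** Take the trigger as p < 0.05 on a baseline t test, and let the adjusted test replace Fisher's when it fires. For the same three strengths, power for 50% vs 25% is 50.2%, 49.2% and 50.1%, practically that of Fisher alone. Type I error is 2.2 to 2.7%. If either test may claim success, it is at most 3.0%.

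**The case against.** The strongest reply is that nothing here is invalid. Fisher's test is standard, prespecified and protected by randomisation, and its sampling error already allows for chance imbalance. With 34 per arm, a difference of more than 0.25 SD in mean eGFR has probability 2 × [1 − Φ(0.25/√(2/34))] = 0.30, which is ordinary. Under the assumed decline model with eGFR uniform on 15 to 60, such a difference moves the failure rate by about 5 points. The standard error of the risk difference is √(2 × 0.5 × 0.5/34) = 12 points at 50% in both arms. All of this stands.

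It also stands that most of the gain may come from replacing Fisher's test: about 10 points from Fisher to the unadjusted LRT in the 50% vs 25% rows, against 2 to 12 from adjustment. The size of the adjustment gain rests on assumed inputs. A condensed article may also leave the covariate list and the cut-off for a difference to a fuller document, so their absence is not the complaint. The complaint is the rule that the article does state.

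Three stronger readings are tempting. A reader might infer that crude and adjusted results compete with no rule for which counts; the article labels the regression secondary, so the crude result is primary. A reader might infer an inflated error rate; with one covariate and a fixed trigger the simulation shows none, though free choice of covariates was not simulated. A reader might take baseline eGFR to be the main determinant of the endpoint; the document does not rank prognostic factors.

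**Conclusion.** The point holds as a matter of efficiency and prespecification. The primary test is valid and conservative. The data-driven choice touches only the secondary adjusted analysis, and the imbalance trigger recovers almost none of the power that routine adjustment would give.

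For 50% vs 25%, the loss is about 6 to 9 points from using Fisher's rather than Boschloo's test, which is an exact calculation. Roughly 2 to 12 further points come from omitting eGFR. That second range is measured against an unadjusted likelihood-ratio test, not against Boschloo's, so the two should not simply be added. It depends on a prognostic strength that the document does not give.

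Even the adjusted analysis reaches only 63 to 72% power with 34 per arm, so the sample-size shortfall at the lower end of the planned effect remains.

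**What to change.** Before unblinding:

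- State that the primary comparison always adjusts for continuous baseline eGFR, whatever the observed balance. Use a logistic model with arm and baseline eGFR, reported as a standardised relative risk with 95% confidence interval.
- Take the p-value from a permutation test that follows the randomisation scheme, to hold 5% in this small sample.
- Delete the rule that makes adjustment depend on noted baseline differences. Any further adjusted analysis should name its covariates on prognostic grounds.
- Keep the unadjusted relative risk as supportive, with Boschloo's test in place of Fisher's.

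The cost is analysis-plan wording and a little code. Baseline eGFR is needed for eligibility, so it should be available for every patient and adds no burden. The plain adjusted likelihood-ratio test may be slightly liberal at this size (up to 5.6% in the simulation above); the permutation p-value removes that.

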### Number of subjects and level of significance

The calculation of the sample size is based on the results of the most comprehensive follow-up of ADPKD patients with advanced kidney disease. With a mean baseline creatinine of 3 mg/dL, or a mean eGFR of 23 mL/min per 1.73 m^2^, respectively, 40.5% of 142 patients showed a doubling of serum creatinine or dialysis after a mean follow-up of 2.3 years [15]. However, with less than 1.5 fold increase instead of 2 fold increase in creatinine we used a stricter criterion for a favorable outcome, and therefore set our expected outcome probability in the control group at 50%. Formally 31 patients in each group are necessary to demonstrate a clinically meaningful reduction of 50 to 90% of the primary endpoint at an α = 0.05 with a power of 80%. To allow for loss to follow-up, we increase this formal sample size by 10%. Therefore we plan to include 34 patients per group or 68 patients overall into our study. Generally a probability (*P*) value of less than 0.05 is considered statistically significant.

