**Table 1 Tab1:** **Subject inclusion and exclusion criteria of the Vienna RAP Study**

**Inclusion criteria**	
	• ADPKD, as confirmed by history, ultrasound, computed tomography or magnetic resonance imaging
	• 18 years of age, or older
	• Baseline eGFR (4-variable MDRD equation) below 60 mL/min per 1.73 m^2^
	• Negative serum pregnancy test prior to administration of sirolimus and agreement to use contraception throughout the study and for three months after
	• Written informed consent

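### The 50% control failure rate comes from a cohort with mean eGFR 23 and is not supported for a trial that admits any eGFR below 60, so neither is the stated 80% power

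*Protocol article*

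**What the plan says.** The planning paragraph (Protocol article, Number of subjects and level of significance) has a single empirical source. It describes that cohort as "With a mean baseline creatinine of 3 mg/dL, or a mean eGFR of 23 mL/min per 1.73" m² and reports that "40.5% of 142 patients showed a doubling of serum creatinine or dialysis after a mean follow-up of 2.3 years". Because the trial counts a rise above 1.5-fold as failure, the authors "therefore set our expected outcome probability in the control group at 50" per cent. No calculation for this step is shown. They conclude that 31 patients per group suffice to "demonstrate a clinically meaningful reduction of 50 to 90% of the primary endpoint at an α = 0.05 with a power of 80" per cent, and add 10% for loss to follow-up to reach 34 per group.

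Eligibility is wider than the cohort's mean suggests. Table 1 requires "Baseline eGFR (4-variable MDRD equation) below 60 mL/min per 1.73" m², and the Aim of the trial and Participants sections use the same ceiling. Apart from the exclusion of patients who need renal replacement therapy there is no lower limit. No stratum, cap or expected mean eGFR is given.

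Under Endpoints, failure is a creatinine rise above 1.5-fold, dialysis, transplantation or death over 2 years. For the primary test, Statistical methods says: "To test the null hypothesis of no difference between the groups we will use the Fisher’s exact test".

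**The concern.** A fold-change in creatinine is a proportional endpoint. The absolute eGFR loss needed to reach it grows with the starting value, so for the same yearly decline a patient starting at 45 or 55 is much less likely to fail within 2 years than one starting at 23. Dialysis within 2 years is also less likely from a higher start. A rate observed around a mean of 23 therefore cannot be carried over unchanged to everyone below 60.

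The paragraph makes no adjustment for baseline eGFR, and none is shown for the shorter follow-up. With a dichotomous endpoint and 31 patients per arm, power depends heavily on the number of control failures. If that number is well below half, a null result could be read as absence of effect when there were too few failures to show one. No interim analysis or early stopping is planned, so nothing in the article would bring a low event rate to light before the end.

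**Working it through.** **Inputs from the article.** Cohort mean eGFR 23; 40.5% doubling or dialysis at a mean of 2.3 years; planned control rate 50%; reduction 50 to 90%; α = 0.05 (taken as two-sided, since sidedness is not stated); 31 per arm; Fisher's exact test; 4-variable MDRD equation; 2-year endpoint.

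**1. The plan's own figure.** Patients per group for 80% power at a 50% control rate:

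| Reduction | Rates | Normal approximation | With continuity correction | Exact Fisher |
|---|---|---|---|---|
| 50% | 50% vs 25% | 58 | 66 | 64 |
| 70% | 50% vs 15% | 27 | 33 | 32 |
| 90% | 50% vs 5% | 15 | 19 | 17 |

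Neither end of the stated range gives 31. A 70% reduction comes closest: exact Fisher power at 31 per arm is 79.7%.

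**2. What a 1.5-fold rise requires.** In the MDRD equation eGFR is proportional to creatinine^(−1.154). The fraction of eGFR kept at a 1.5-fold rise is 1.5^(−1.154) = 0.626, so the yearly loss over 2 years is baseline × (1 − 0.626)/2:

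- from 23: 8.6/2 = 4.3 mL/min per year
- from 45: 16.8/2 = 8.4
- from 55: 20.6/2 = 10.3

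Simple inverse proportionality (loss of one third) gives 3.8 from 23 and 7.5 from 45, so the pattern does not depend on the exponent.

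**3. An illustrative control rate (assumptions).** Assume linear eGFR loss, normally distributed between patients with SD 2 to 4 mL/min per year, the same at every baseline. Calibrate it so that a patient at eGFR 23 has a 40.5% chance of doubling by 2.3 years. Doubling keeps 2^(−1.154) = 0.449 of eGFR, a loss of 23 × 0.551/2.3 = 5.51 per year. The mean loss is then 5.51 − 0.240 × SD, which is 5.0 for SD 2 and 4.5 for SD 4. Dialysis, transplantation and death are not modelled separately.

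The 2-year failure probability is 1 − Φ((baseline × 0.374/2 − mean)/SD):

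| Baseline eGFR | Probability over SD 2 to 4 |
|---|---|
| 23 | 52-64% |
| 30 | 39-40% |
| 40 | 11-23% |
| 45 | 5-17% |
| 55 | 0-8% |
| uniform 20-40 | about 40% |
| uniform 15-45 | 40-41% |
| uniform 15-60 | 28-30% |

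**4. Exact Fisher power at 31 per arm**, by full enumeration:

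| Reduction | Control 50% | 40% | 30% | 20% |
|---|---|---|---|---|
| 50% | 44% | 31% | 20% | 10% |
| 70% | 80% | 64% | 44% | 22% |
| 90% | 99% | 93% | 77% | 43% |

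**The case against.** The strongest reply is that eGFR below 60 is only a ceiling. The title speaks of advanced disease, and the pilot study from the same clinic (Assessment of safety) enrolled eGFR 20 to 40, so the trial may in practice recruit a mean near 23. At 23 the model above returns 52-64%, which is no lower than the planned 50%. The model is also crude: it places every source patient at exactly 23, applies one absolute decline at all baselines, and leaves out three of the components that count as failure. The article gives no event rate or yearly decline for eGFR 30 to 60.

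Much of this stands. A reader might infer that the planned power is definitely absent, or that even a very large effect would be missed. The article supports neither: no baseline distribution is given, and a 90% reduction, which lies within the planned range, keeps 77% power at a 30% control rate and 93% at 40%. Nor does the shorter follow-up by itself show that 50% is too high. Under a constant hazard 40.5% at 2.3 years becomes 1 − 0.595^(2/2.3) = 36% at 2 years, but that concerns doubling, not the 1.5-fold threshold. Finally, the eGFR mismatch does not explain the whole shortfall: for a 50% reduction, power is only 44% even at the planned 50% rate.

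The reply does not supply a justification for the rate. The article never says that a mean near 23 is expected, and a spread of 20-40, the pilot's own range, already brings the modelled rate down to about 40%.

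**Conclusion.** The concern holds in a conditional form. The 50% control rate is an extrapolation from a mean eGFR of 23 to a population bounded only at 60, without adjustment for baseline eGFR. It is not supported for that population and is probably too high unless the enrolled mean is near 23. The direction follows from the proportional endpoint. The size rests on the linear-decline model and on assumed baseline distributions, which put the rate at about 40% (15-45) or 28-30% (15-60).

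At those rates, power for a 70% reduction is about 64% or a little under 44%, against 80% at the planned rate. For a 50% reduction, the size named under Endpoints, it is about 31% or roughly 20%, from a starting point of 44%. The claim of 80% power across reductions of 50 to 90% should not stand as written.

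**What to change.** Restate the planning paragraph so that it:

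1. says that the 50% control rate presumes a mean baseline eGFR near 23;
2. names the single effect that 31 per arm can detect with 80% power, about a 70% reduction at a 50% control rate, in place of the range;
3. tabulates exact Fisher power for control rates of 20 to 50%, as in step 4;
4. checks the assumed rate against the blinded baseline eGFR distribution of patients already enrolled.

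The last step needs no outcome data and no unblinding. A blinded count of failures would add little: the endpoint is read at month 24, and with first enrolment on 28 April 2014 nobody had completed follow-up when the article appeared in April 2015. A report of achieved power would add nothing to the planned relative risk with its 95% confidence interval. No change to eligibility is needed for this correction.

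The cost is a revised paragraph and one blinded tabulation. The downside is that the stated power becomes less favourable.

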### Endpoints

The primary endpoint is a 50% reduction in the doubling of serum creatinine, or initiation of dialysis, renal transplantation, or death over a period of 2 years. A 1.5-fold or lower increase in serum creatinine without initiation of dialysis, renal transplantation, or death over 2 years is considered a beneficial outcome; increases in serum creatinine greater than 1.5 over 2 years or initiation of dialysis, renal transplantation, or death are considered a non-beneficial outcome. Secondary endpoints are safety, change in proteinuria (as indicated by albumin/creatinine- and protein/creatinine ratio, respectively), and creatinine clearance.

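### The stated 80% power with 31 patients per group holds only from about a 70% reduction upward; at the 50% reduction also called clinically meaningful it is about 44%

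*Protocol article*

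**What the plan says.** The section on number of subjects and level of significance starts from a published cohort in which 40.5% of 142 patients had a doubling of creatinine or dialysis. Because the trial counts a smaller creatinine rise as failure, the authors "set our expected outcome probability in the control group at 50" per cent. The size claim follows: "Formally 31 patients in each group are necessary to demonstrate a clinically meaningful reduction of 50 to 90% of the primary endpoint at" α = 0.05, with 80% power. The figure is raised by 10% for loss to follow-up, to 34 per group and 68 in all.

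The test is fixed under Statistical methods: "To test the null hypothesis of no difference between the groups we will use the Fisher’s exact test". The effect is to be reported as a relative risk with a 95% confidence interval. Sidedness is not stated in words.

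The Endpoints section also mentions a halving: "The primary endpoint is a 50% reduction in the doubling of serum creatinine", followed by dialysis, transplantation or death. No single design effect between 50% and 90% is given anywhere.

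**The concern.** A sample size belongs to one effect. With control failure at 50%, the stated range runs from 50% vs 25% to 50% vs 5%, an absolute difference of 25 to 45 percentage points. The required number falls steeply over that span, so 31 cannot be the number needed at both ends.

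The lower end matters most. The article counts a 50% reduction as clinically meaningful, so a reader will take it that the trial has an 80% chance of detecting a drug that halves the failure rate. If the true chance is well under that, the funder, the ethics committee and later readers have been given a wrong picture of what the trial can show.

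**Working it through.** **Inputs.** Control failure 50%; relative reduction 50% to 90%; α 0.05; power 80%; 31 per group, 34 after inflation (all from the sample size section). Fisher's exact test (Statistical methods). Two-sided testing is an assumption, taken from the null hypothesis of no difference; one-sided results are shown as well.

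**Step 1. Try to reproduce 31.** The usual two-proportion formula with pooled variance under the null is

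n = [1.96·√(2·p̄·q̄) + 0.8416·√(p₁q₁ + p₂q₂)]² / (p₁ − p₂)²

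- 50% vs 25%: p̄ = 0.375. n = [1.96·√0.46875 + 0.8416·√0.4375]² / 0.25² = (1.342 + 0.557)² / 0.0625 = 57.7, so 58 per group (66 with continuity correction).
- 50% vs 5%: p̄ = 0.275. n = [1.96·√0.39875 + 0.8416·√0.2975]² / 0.45² = (1.238 + 0.459)² / 0.2025 = 14.2, so 15 per group (19 with correction).
- One-sided, the same ends need 46 and 12 (54 and 16 with correction).

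Neither end gives 31. Reading the range as favourable-outcome rates of 50% vs 90% gives 20 (25 with correction), which fails too.

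Effects inside the range do come close. At 50% vs 15% (70% reduction) the continuity-corrected number is 33, and exact Fisher power with 31 is 79.7%. Other inputs also return 31: a one-sided uncorrected test at a 60% reduction, a one-sided corrected test at 65%, or a two-sided uncorrected test with a 40.5% control rate and a 75% reduction. The origin of 31 therefore cannot be settled from the article.

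**Step 2. Exact power of the planned test.** For independent binomial counts X ~ Bin(n, 0.50) and Y ~ Bin(n, p₂), power is the sum of P(X = i)·P(Y = j) over all tables (i, j) with Fisher p < 0.05.

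| Relative reduction | Treated failure | Two-sided, 31 per group | Two-sided, 34 per group | One-sided, 31 per group |
|---|---|---|---|---|
| 50% | 25% | 43.7% | 49.3% | 55.3% |
| 60% | 20% | 62.0% | 67.9% | 73.1% |
| 65% | 17.5% | 71.2% | 76.3% | 80.9% |
| 70% | 15% | 79.7% | 83.7% | 87.5% |
| 75% | 12.5% | 86.9% | 89.9% | 92.6% |
| 80% | 10% | 92.5% | 94.5% | 96.1% |
| 90% | 5% | 98.6% | 99.2% | 99.4% |

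At a 71% reduction, 31 per group gives 81.2%, so the two-sided power crosses 80% between 70% and 71%.

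**Step 3. Can another reading reach 80% at a 50% reduction?** The uncorrected normal approximation with 31 per group gives Φ[(0.25·√31 − 1.342)/0.661] = Φ(0.076) = 53.0%; one-sided it gives 65.6%. One-sided Fisher with all 34 per group gives 60.8%. None reaches 80%.

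**Step 4. Number needed for a halving.** Two-sided Fisher power for 50% vs 25% is 79.4% with 63 per group and 80.2% with 64. So about 64 evaluable patients per group are needed, roughly twice 31.

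**Sensitivity to the control rate.** If control failure were the 40.5% of the source cohort, two-sided Fisher power with 31 per group would be about 32% for a 50% reduction and 65% for a 70% reduction. The conclusion does not depend on this.

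**The case against.** The strongest defence is that 31 per group fits a 70% reduction under Fisher's test, and 70% is the midpoint of the stated range. The trial may have been sized for a mid-range effect, with the plausible range printed in place of the design value. That would be a fault of wording, and the design would be coherent for a large effect. This is plausible and stands as a possibility, but it is an inference: other inputs give 31 equally well, and the sentence as printed still attaches 80% power to effects that do not have it.

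The claim is also not wrong throughout. A reader might infer that 80% is reached only near the middle of the range. It is not so: power is close to 80% at a 70% reduction and rises above it all the way to 90%.

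The analysed number may lie nearer 34 than 31, since the intention-to-treat set takes in everyone with a single exposure, and dialysis, transplantation and death count as failures. At 34 the chance of detecting a halving is about even (49.3%), still far below 80%.

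A further inference would be that any non-significant result must be called inconclusive for reductions below about 70%. The article does not support that. It plans a relative risk with a 95% interval, and the interval can say more than pre-trial power. For example, if about half of 31 fail in each arm, the standard error of the log relative risk is √[2·(1/15.5 − 1/31)] = 0.254, and the interval is exp(±1.96·0.254), about 0.6 to 1.6, which already excludes a halving.

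Lastly, the halving in the Endpoints section is weak support. It sits in an awkward definition that then moves to a 1.5-fold criterion, and it need not be a design effect. The point does not need it, because the sample size section itself includes 50% in the clinically meaningful range.

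**Conclusion.** The concern holds as a wrong statement of power. With a 50% control failure rate and a two-sided Fisher exact test at 0.05, the claimed 80% with 31 per group is true from about a 70% reduction upward and false below it. At the low end of the stated range the shortfall is about 36 percentage points (80 − 43.7), or about 31 points if all 34 are analysed (80 − 49.3). A drug that truly halved failures would go undetected 56% of the time with 31 evaluable per group.

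The result rests on two assumptions: the article's own 50% control rate, and two-sided testing. One-sided testing moves the threshold down to about a 65% reduction but leaves the lower end short.

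The documents do not show that the sponsor designed for 70%, that the trial must be enlarged, or that a null result will be misread. They do show a power figure that cannot be right over the range it is attached to.

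**What to change.** In the section on number of subjects, replace the range with:

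> With a control failure rate of 50%, 31 evaluable patients per group give about 80% power (two-sided Fisher exact test, alpha 0.05) for a reduction to 15% (70% relative reduction) and about 44% power for a reduction to 25% (50% relative reduction).

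The sponsor should add the single effect size, and the sidedness, actually used to obtain 31. The 70% in this sentence describes what 31 per group can detect and should not be presented as the original assumption unless the sponsor confirms it.

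Carry the same statement into the trial report, and interpret a non-significant result from the planned relative risk and its 95% confidence interval, with no label set by a pre-trial power threshold.

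The cost is one corrected sentence and one clarification. Sample size, endpoint, test and conduct stay as they are; the stated power becomes less favourable for a halving.
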